**Fig 3 pone.0291067.g003:**
[figure not shown]
Schematic illustrating the care transition intervention and treatment-as-usual.

We developed the CTI based on a thorough review of the literature (MEDLINE and Google Scholar with the search term “mental health treatment engagement" and no filters) finalized on February 8th, 2022. The literature was reviewed by a group of experts of different backgrounds (psychiatrist, epidemiologist, psychologist). Specifically, we selected the intervention components with respect to their potential effectiveness for increasing mental health treatment engagement accounting for the five WHO domains for factors influencing treatment engagement and adherence (see Table 1 for details).

**Table 1 pone.0291067.t001:** Study conceptual framework.

WHO Domain for Factors Influencing Treatment Engagement and Adherence	AMBITION Intervention	
	Specific Targets	Strategies or techniques
**Social and Economic**	Socioeconomic status	Readily accessible technology-facilitated intervention
	Employment and education	Low-threshold intervention compatible with work- and family-related obligations
	Health literacy	Use of well comprehensible educational material and graphical instructions
	Social support	Provision of emotional support
	Treatment costs	Intervention at no cost (covered by funding in the pilot stage)
	Racial, ethnic, gender, and cultural background	Attentiveness for diversity and gender-specific healthcare-seeking behaviours
**Healthcare System**	Shortage of community mental health services	Active support in seeking treatment
	Fragmentation of care	Intervention at the time of great risk for discontinuity of care
	Patient-centred care	Fostering informed conversations between providers and patients
**Therapy-related**	Complexity	Psychoeducation on potential types of treatment and treatment duration
	Previous treatment failures	Exploration of previous treatment experiences (e.g., summary of inpatient / day clinic stay)
	Unintended consequences and adverse effects	Exploration of potential treatment adverse effects in the past
**Patient-related**	Health beliefs	Deepening the understanding for the respective mental health disorder
	Perceived barriers	Systematic identification and optimised removal of barriers
	Treatment engagement-related needs	Behavioural strategies for improving treatment engagement
**Condition-related (depressive disorders)**	Feelings of hopelessness	Fostering change expectancy
	Loss of interest and/or pleasure	Behavioural activation
	Rumination	Behavioural activation

### Intervention

We will not provide psychotherapy focused on direct symptom improvement during the intervention aim of the CTI is to empower and support the patient to take up follow-up treatment (e.g. seeking a guideline-based adequate follow-up care in the form of remission-stabilising maintenance therapy). The CTI will be delivered by a CTN and is composed of core components and optional components. Core components have been shown to be effective in increasing mental health treatment engagement in previous work, which will be the primary outcome in sufficiently powered confirmatory trial after this pilot. Hence, core components are compulsory parts of the intervention. The optional components will be used as needed by the CTN to provide more individualised guidance and support to each patient. The type and design of the outpatient psychosocial follow-up treatment will primarily be based on the recommendations of the case leading therapist on the ward / day clinic. The first core component is the identification and subsequent addressing of barriers that prevent the patient from taking up an outpatient psychosocial follow-up treatment [29, 30]. The CTN will use motivational interviewing and psychoeducation to encourage the patient to make and keep appointments with outpatient mental health services. The patient, supported by the CTN, will develop a summary of the inpatient stay from her or his own perspective. This enables the CTN to identify both challenges and achievements from the patient’s point of view and to address the respective challenges more precisely in further joint work that includes emotional support for the patient (core component 2) [31]. For example, the type of outpatient follow-up treatment can be adapted based on factors which have already contributed to improvements for the patient during their inpatient stay. In preparation for the intervention, the CTN will receive extensive study-related training in motivational interviewing, diversity, and gender-specific healthcare-seeking behaviours and social work topics (core component 3) [32, 33]. The CTN will be a research assistant with a bachelor’s degree in psychology. These steps will take place during the first joint appointment (CTI session) before the patient is discharged.

After discharge, further CTI sessions will take place between the patient and the CTN, during which barriers on the patient’s side will be continuously identified and addressed. Additionally, if necessary the CTN will reflect on the ambivalence towards follow-up treatment with the patient, to build motivation. In the first month after discharge, there will be two CTI sessions; in the months two and three after discharge, there will be one CTI session per month. If a patient successfully takes up outpatient follow-up treatment before the fifth CTI session, at least one further CTI session will be offered for joint final reflection and assessment of the sustainability of follow-up treatment. If the patient needs more structuring of the intervention, a patient-centred written brief discharge plan will be jointly developed by the patient and the CTN. This will help to (1) clarify the need and (2) the desired design of a follow-up treatment, (3) identify possible barriers, (4) identify patient’s areas/problems in particular need of support by the CTN, and (5) schedule the session dates between patient and CTN (1^st^ month two sessions, 2^nd^ and 3^rd^ month one session each). To support and motivate the patient, the CTN can screen for psychosocial services and treatment possibilities in the vicinity of the patient’s home. Furthermore, the patient will be motivated to contact the general practitioner after discharge and to inform him/her about the further course of treatment. Further components for support and motivation can vary individually depending on the symptom severity and the resources of the patient, but will include components of the following spectrum: systematic reminders about doctor’s appointments and medication intake, screening for suicidal ideation, evaluation of already known and/or newly emerging barriers, psychoeducation regarding the handling of mental disorders and coping strategies and behavioural activation (maintaining a positive attitude, solution orientation, stimulation of self-help). These optional components have been shown to be effective in several comparable studies [14, 17]. The CTI sessions will be conducted via a secure (i.e., encrypted), web-based videoconferencing platform on a subscription basis (arztkonsultation ak GmbH) and will last between 30 and 60 minutes. Subscription fees are covered by the trial funding. No fee will apply for patients. In routine care in Germany, the use of teleconferencing systems is covered by the statutory health insurance. During the intervention period, the CTN will attend a case supervision session led by a senior physician every two weeks, where all patients will be discussed. In particular, it will be discussed how to deal with hard-to-reach and less adherent patients to successfully implement the transition to outpatient psychosocial follow-up treatment in this group as well.

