### Outcomes

As this is a feasibility trail, there will be no hypotheses or statistical testing. Therefore, effects of the intervention are not to be expected in this small sample. Instead, we expect that a) our trial design (incl. study procedures such as recruitment strategy, data collection procedures, randomisation and logistic aspects) is suitable and b) that the intervention is feasible in this population of inpatients and at this specific time point during treatment, the transition from inpatient to outpatient care.

The feasibility of a subsequent large-scale RCT for patients at the transition from inpatient to outpatient care will be determined by assessing the following outcomes and aspects [34]:

■ recruitment strategy’s sufficiency and efficiency for both groups■ adherence for intervention group■ feasibility of study procedures (e.g., patient and provider acceptance of randomisation and outcome measurements)■ intervention procedure feasibility (CTN documentation, patient acceptance of CTI, patient safety)

To estimate the sufficiency and efficiency of the recruitment strategies, we will calculate the recruitment yield, i.e., number randomized per number screened, and the consent rate, i.e., number randomized per number eligible. We will record retention rates and reasons for non-participation or dropping out. Adherence will be determined by the ratio of scheduled and actually conducted CTI session. Concerning documentation, after every CTI session, the CTN will systematically document which elements of the intervention were used in the respective session. Patients experience relapses will have full and free access to all levels of mental healthcare which covered under the statutory health insurance in Germany. We will approach all patients systematically for post assessments regardless of whether they have received a relapse to minimize missing data for the follow-up. To evaluate process outcomes on the overall practicability of the intervention and the related study procedures, we will draw on qualitative data generated by in-depth interviewing of patients and the CTN.

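### Suicidal-ideation screening is an optional CTI component used as needed by the navigator, so the article does not ensure that every CTI patient is asked after discharge

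*Protocol article*

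**What the plan says.** The protocol article, section Intervention, sorts the CTI into two classes. On the first it says: "Hence, core components are compulsory parts of the intervention". On the second: "The optional components will be used as needed by the CTN to provide more individualised guidance and support to each patient".

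Later in the same section it introduces the second class again: "Further components for support and motivation can vary individually depending on the symptom severity and the resources of the patient". The list that follows contains "medication intake, screening for suicidal ideation, evaluation of already known and/or newly emerging barriers", and the next sentence calls the listed items optional.

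Three core components are named: work on barriers ("The first core component is the identification and subsequent addressing of barriers"), the patient's own summary of the stay together with emotional support, and the navigator's training. The navigator is a research assistant qualified to bachelor level in psychology.

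One session takes place before discharge. After it, "In the first month after discharge, there will be two CTI sessions", then one in each of the next two months. For oversight, "the CTN will attend a case supervision session led by a senior physician every two weeks, where all patients will be discussed".

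The Outcomes section lists "intervention procedure feasibility (CTN documentation, patient acceptance of CTI, patient safety" among the aspects to be assessed. It also has the navigator document after each session which elements were used.

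**The concern.** The Introduction counts a higher suicide risk among the consequences of care that breaks off between inpatient and outpatient treatment. The CTI covers exactly that period. Under Inclusion and exclusion criteria, the trial enrols inpatients treated for at least moderate depression and/or anxiety and excludes those returning to outpatient psychotherapy begun before admission. Suicidality is not among the exclusion criteria.

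The only suicide-risk check that the article names within the CTI is the screening item, and whether a given patient is asked depends on how the navigator judges that patient's need. Choosing whom to ask by apparent severity presupposes part of what the question is meant to find out. A patient who seems to be coping may not be asked. At stake is the safety of individual patients in the CTI arm, and how well a pilot that names patient safety as a feasibility aspect can speak to it.

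**Working it through.** This is mainly a question of what the text requires. Arithmetic enters only for scale and cost.

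**Step 1: is screening compulsory anywhere?**

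| Element in the optional list | Required elsewhere in the article? |
|---|---|
| Evaluation of known or new barriers | Yes: first core component, and continued after discharge (Intervention) |
| Screening for suicidal ideation | No: not among the three core components, nor in Outcomes, Measurements, or Ethics and dissemination |

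The overlap for barriers shows that appearing in the list does not by itself make an element discretionary. For barriers, another sentence supplies the requirement. For suicidal-ideation screening there is no such sentence, so the optional status stands.

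**Step 2: do the other safeguards make the check universal?**

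- Supervision covers all patients, but can discuss only what was asked or volunteered.
- Post-session documentation records use and does not require it.
- Access to all levels of care for relapsing patients (Outcomes) is treatment, not detection.
- Questionnaires are next repeated three months after inclusion (Patients' health status). The article does not say whether any of them asks about suicidality, and nothing here relies on that.

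**Step 3: how many patients and sessions?**

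- Inputs: N = 50 (Sample size), 1:1 allocation (Randomisation), session schedule (Intervention).
- CTI arm: 50 × 1/2 = 25. If allocation were simple randomisation (an assumption, as block use is not stated), the 95% range is 18 to 32.
- Sessions per patient: 1 + 2 + 1 + 1 = 5, which agrees with the abstract; 4 of them follow discharge.
- Sessions in all: 25 × 5 = 125 at most, of which 25 × 4 = 100 follow discharge. Early uptake of treatment can shorten a patient's series.

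The number of CTI patients who will be asked can lie anywhere from 0 to 25. That none is guaranteed is only what optional means; it is not an estimate of coverage.

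**Step 4: what would a compulsory question cost?**

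Navigator time = sessions × minutes per session. The minutes are assumed.

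| Assumed minutes | 125 sessions | Hours |
|---|---|---|
| 2 | 250 min | 4.2 |
| 3 | 375 min | 6.25 |
| 5 | 625 min | 10.4 |

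Three minutes take 3/60 = 5% to 3/30 = 10% of a session planned at 30 to 60 minutes.

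Physician time = sessions × share positive × minutes per contact. With an assumed 5% to 20% positive and an assumed 20 minutes each, 125 × 0.05 = 6.25 to 125 × 0.20 = 25 contacts, that is 125 to 500 minutes, or about 2 to 8 hours.

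**The case against.** The strongest reply is that a journal article condenses the full protocol. The screening item sits in a list of components for support and motivation, so it is intervention content and need not be the trial's safety procedure. Core status is reserved for components shown to raise treatment engagement, and a suicide screen is not core by that criterion. A separate procedure may exist in the full protocol or the ethics file. All of this is fair, and it limits the point: the article cannot be faulted for lacking a crisis plan. It does not remove the point, because the article is not silent here. It states the status of the in-session screen, and that status is optional.

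Second, discretion is not unguided. Use varies with symptom severity, a senior physician discusses every patient at regular intervals, elements used are documented, and patients are encouraged to see their general practitioner. These make it likely that many patients are asked. They do not ensure that each one is.

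Third, there is no contradiction between naming patient safety as an aspect and leaving one component to judgement. That is correct; this is a design choice that could be better fixed, not an error.

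Fourth, control patients face the same period, and a change within the CTI does nothing for them. That stands as a limit of the remedy. Screening is already part of the CTI, so making it uniform adds no new component to one arm.

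Fifth, the article expects recruitment to end in September 2023 and data collection by May 2024, so the change may come too late for this trial. That too may stand, and the recommendation then carries over to the main trial.

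**Conclusion.** The point holds as a limited one. By its own wording the article leaves suicidal-ideation screening to the navigator's judgement, so it does not ensure that each of about 25 CTI patients is asked during the months after discharge. It rests on the stated split between compulsory and optional components and on the absence of any sentence that makes this item compulsory. The arm size assumes the target of 50 is reached and splits evenly.

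A reader might infer more, and the article does not support it:

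- **That patients will go unscreened.** The text leaves coverage open; it may be high.
- **That a positive answer would wait for the next supervision session.** The article neither says so nor rules out earlier contact, and the route for positive answers may be set out in the full protocol.
- **That the trial's figure for suicidal ideation would be biased by selective asking.** Neither Outcomes nor Data analysis plans such a count.

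The change is worth making because it is cheap and concerns patient safety in a period that the article itself links to raised risk.

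**What to change.** Move a brief scripted suicidal-ideation question from the optional list to the compulsory elements of each CTI session, including the one before discharge. Then:

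- record whether it was asked (yes/no) and the result on the existing post-session documentation;
- handle positive answers through the existing supervising senior physician role, under the trial's safety procedure;
- report the number of CTI patients asked and the number positive, descriptively and for the CTI arm only.

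If sessions are under way, apply this to those that remain; if they are complete, apply it to the main trial.

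The cost is a few minutes per session, at most about 6 hours of navigator time for 25 patients under the 3-minute assumption, within sessions already planned. Physician time for positive answers comes on top and depends on the unknown share positive. A short navigator briefing is needed, one entry is added to the documentation, and an ethics amendment is needed if the trial is running. There are no extra patient visits.

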
### Control condition

Patients allocated to the control group will receive the usual support by their case leading therapist on the ward in their search for outpatient psychosocial follow-up treatment (e.g. by being given contact details of outpatient psychotherapists in the vicinity and motivated to make contact during the further course of inpatient treatment). This will also include participating in a follow-up supportive group provided by the inpatient staff (five sessions for each patients) after patients have been discharged. This open group meets once a week to discuss problems in organising follow-up treatment and to provide rather general than individualised support.

### Sample size

In this study, we aim to establish feasibility of a full trial and not to provide evidence of a statistically significant difference concerning effectiveness between the two treatment conditions. Therefore, we did not perform a formal sample size calculation [34–36]. Instead, our target sample size of *N* = 50 participants is based on the recommendations for conducting pilot and feasibility trials as described by the National Institute for Health Research [37].

### Recruitment

Patients will be recruited during their inpatient / day clinic stay in mental healthcare departments of German Hospitals. Suitable patients will be approached by their case leading therapist on the ward / day clinic during the regular therapy sessions three weeks prior to discharge. Here they will be informed about the study and provided with the study documents, consisting of information leaflet and the consent form in duplicate. If the patient agrees to receive further information, they will have a meeting with the CTN two weeks prior to discharge. During this meeting the CTN will 1) describe the study procedures to the patient, 2) address any remaining questions the patient may have, 3) obtain written informed consent, 4) collect the patient’s baseline data (either by filling out the questionnaire or through an online assessment), 5) allocate the patient to one of the two study conditions via an online randomisation platform, 6) inform the patient of the outcome of the randomisation, and, 7) if randomised to the intervention condition, arrange a first appointment (CTI session), which must still take place during the inpatient stay. If inclusion in the study is not possible, this will be documented with the reason and the patient’s age and gender. The CTN informs the case leading therapist on the ward of the outcome result of the randomisation.

### Randomisation

After obtaining informed consent, patients will be randomly allocated to one of the two study conditions (treatment-as-usual, TAU vs. care transition intervention) in a 1:1 ratio. To ensure a seamless inclusion process, the CTN will conduct the randomisation during the initial recruitment meeting with the patient and subsequently inform the patient of the outcome. Concealment of the treatment sequence up to allocation will be assured via a secure web-based randomisation system (Randomizer, https://randomizer.at) operated by a data manager, not involved in the patient recruitment, centrally at the Department of General Internal Medicine and Psychosomatics, Heidelberg University. The treatment sequence is generated through a computer-generated sequence of random numbers. Randomisation will be stratified by depression and anxiety symptom severity at baseline as measured with the PHQ-ADS (three levels: minimal/mild, moderate, severe).

### Measurements

This study will assess the feasibility and acceptance of both the CTI and study procedures, such as data collection, as it would occur in a sufficiently powered effectiveness trial. We will, therefore, evaluate if the procedures are appropriate for this specific patient group as well as collect data on clinical endpoints.

### Patients’ health status

For patients, the baseline assessment will take place right before randomisation. This includes variables on sociodemographic information, patient’s history of outpatient as well as inpatient mental health treatment and history of psychopharmacotherapy. Data will be collected using the validated questionnaires: Patient Health Questionnaire Anxiety and Depression Scale (PHQ-ADS) [24], 12-Item Short-Form Health Survey (SF-12) [25], Recovery Assessment Scale (RAS-G) [26], Somatic Symptom Disorder–B Criteria Scale (SSD-12) [27]. Since the aim of this study is to enable patients to organise their treatment following an inpatient stay and ideally take up outpatient psychosocial treatment, we will comprehensively record service use regarding such treatment options. Post and follow-up measurements will be conducted three, six and nine months respectively after study inclusion and will include the same validated questionnaires and service use assessments as at baseline. At this pilot stage, we will not account for the intensity of the treatment received prior to enrolment, since we are primarily interested in feasibility outcomes. However, in the sufficiently powered main trial, we will assess this variable applying the Questionnaire for the Assessment of Medical and non-Medical Resource Utilisation in Mental Disorders (FIMPsy) [38]. Research assistants will conduct the post and follow-up measurement in Computer Assisted Telephone Interviews (CATIs) with the participants. The study schedule is depicted in Fig 3 in line with the SPIRIT guidelines.

